## Abstract

**Background:**

Despite the health benefits of physical activity, data from the UK suggest that a large proportion of adolescents do not meet the recommended levels of moderate-to-vigorous physical activity (MVPA). This is particularly evident in girls, who are less active than boys across all ages and may display a faster rate of decline in physical activity throughout adolescence. The ‘Girls Active’ intervention has been designed by the Youth Sport Trust to target the lower participation rates observed in adolescent girls. ‘Girls Active’ uses peer leadership and marketing to empower girls to influence decision making in their school, develop as role models and promote physical activity to other girls. Schools are provided with training and resources to review their physical activity, sport and PE provision, culture and practices to ensure they are relevant and attractive to adolescent girls.

**Methods/Design:**

This study is a two-arm cluster randomised controlled trial (RCT) aiming to recruit 20 secondary schools. Clusters will be randomised at the school level (stratified by school size and proportion of Black and Minority Ethnic (BME) pupils) to receive either the ‘Girls Active’ intervention or carry on with usual practice (1:1). The 20 secondary schools will be recruited from state secondary schools within the Midlands area. We aim to recruit 80 girls aged 11–14 years in each school. Data will be collected at three time points; baseline and seven and 14 months after baseline. Our primary aim is to investigate whether ‘Girls Active’ leads to higher objectively measured (GENEActiv) moderate-to-vigorous physical activity in adolescent girls at 14 months after baseline assessment compared to the control group. Secondary outcomes include other objectively measured physical activity variables, adiposity, physical activity-related psychological factors and the cost-effectiveness of the ‘Girls Active’ intervention. A thorough process evaluation will be conducted during the course of the intervention delivery.

**Discussion:**

The findings of this study will provide valuable information on whether this type of school-based approach to increasing physical activity in adolescent girls is both effective and cost-effective in the UK.

**Trial registration:**

ISRCTN10688342. Registered 12 January 2015.

## Background

Physical activity has been associated with numerous physiological and psychological benefits for young people [1, 2]. Despite this, a large proportion of children and adolescents do not meet UK recommended physical activity guidelines of at least 60 min of moderate to vigorous physical activity (MVPA) every day [3]. Self-reported data from the Health Survey for England reports that only 18 % of young people aged 5–15 years meet the recommended guidelines. Furthermore, declines in MVPA are evident during and following the transition to secondary school (age 11+ years) when a significant drop in the number of both boys and girls meeting MVPA guidelines is observed, with the drop often being steeper in girls. For example, at age 5 to 7 the same proportion of boys and girls meet recommendations (~24 %) but this declines to 14 % in boys and 8 % in girls by age 13 to 15 [4].

UK adolescent girls cite a number of personal factors (body image, embarrassment, skill), perceptions about physical activity (too competitive, not fun) and a perceived lack of support (limited opportunities and provision designed for girls, boys getting more support) as barriers to being active [5]. These issues tend to be exacerbated as girls move through adolescence [5], a time when dramatic changes in physical maturation has psychological and social impact that could contribute to girls’ disengagement from physical activity [6]. Due to the pronounced gender differences in physical activity levels, developing physical activity interventions and strategies that are sensitive to girls’ needs and interests is a challenging priority [7].

To date, a variety of settings and methods have been used to encourage physical activity in young people, including alterations to the school cultural or physical environment, modifying the school curriculum, adding extra physical activity within the school day, and interventions with a community or family component [8–11]. Reviews to date have struggled to draw general conclusions on the effectiveness of physical activity interventions among girls due to inconsistent findings, but several strategies have consistently emerged as being associated with enhanced efficacy. For example, interventions appeared to be most effective when they were school-based, included enjoyable physical education (PE) as a main component (i.e., making PE more enjoyable for girls by increasing choice and non-competitive and innovative activities) and promoted positive peer relationships through peer tutoring or peer modelling and social support of friendships groups in physical activity settings [8, 11]. Other research has also suggested that as children move into adolescence, peers become a strong influence on physical activity [12, 13]. One review identified only two peer based interventions aimed at young girls; suggesting that future research is needed to evaluate these types of programmes especially when implemented with older girls [8]. Reviews identified limitations in the methodological quality of the evaluation such as lack of high quality randomised controlled trials, lack of precision of the physical activity outcome measures and small sample sizes [8, 11]. Furthermore, the majority of school-based evidence comes from North America and elsewhere [9, 10, 14–20] and differences in infrastructure, school systems and culture make it inappropriate to translate these directly to the UK [8, 11, 21]. There is a small evidence base for school based interventions in the UK but this is limited and focuses mainly on primary schools [22–27], or increasing activity solely during PE classes [28, 29].

This study seeks to build on previous successful school-based interventions by robustly evaluating through a randomised controlled trial a school-based intervention (Girls Active) which focuses on increasing adolescent girls’ physical activity, sport and PE participation through peer leadership and marketing and engaging girls in decision making within the school for physical activity, sport and PE provision. A wider whole school approach through training for teachers, teachers reviewing current physical activity, PE and sport provision for girls, setting action plans and on-going mentoring for schools is also incorporated.

### Aim and objectives of the study

#### Aim

To investigate whether ‘Girls Active’ is effective and cost-effective in promoting increased physical activity in adolescent girls.

### Primary objective

To investigate whether ‘Girls Active’ leads to higher objectively measured moderate-to-vigorous physical activity (MVPA) in adolescent girls aged 11–14 years at 14 months after baseline assessment compared to the control group.

### Secondary objectives

2.To investigate whether ‘Girls Active’ results in changes to the following outcomes at 7 and 14 months after baseline assessment:Increases in objectively measured total volume of physical activity.An increase in the proportion of girls meeting MVPA guidelines (measured objectively).Increases in objectively measured MVPA.Reductions in time spent sedentary (measured objectively and self-reported).Reductions in measures of adiposity (body mass index percentile, percent body fat).Improvements in psychological factors that may mediate physical activity participation (attitudes to physical activity, enjoyment of physical activity, motivation and confidence to be active, activity-related social support, physical self-perceptions).3.To determine the cost-effectiveness of the ‘Girls Active’ intervention.

## Methods

### Design

This study is a two-arm cluster randomised controlled trial (RCT) aiming to recruit 20 secondary schools. Clusters will be randomised at the school level. The 20 secondary schools will be recruited from state secondary schools within the Midlands area (i.e., Leicestershire, Nottinghamshire, Derbyshire and Warwickshire). We aim to recruit 80 girls aged 11–14 years in each school. Figure 1 shows the flow of schools and participants through the study.

**Fig. 1 Fig1:**
[figure not shown]
Flow diagram of study

This study will be conducted, analysed and reported according to the Consolidation Standards of Reporting Trials (CONSORT) statement for cluster RCTs [30]. Ethical approval has been sought and obtained from the University of Leicester ethical representative and the University of Leicester will act as study sponsor.

### School recruitment

All state secondary schools in Leicester, Leicestershire and Rutland with girls aged 11–14 years (*n* = 56) will be invited to take part in the study along with a small number of other state secondary schools along the M1 corridor in Derbyshire, Nottinghamshire and Warwickshire. Eligible schools will be sent an initial letter outlining the ‘Girls Active’ intervention and the evaluation and inviting them to a briefing event. At the briefing event the teachers will receive a detailed presentation about the ‘Girls Active’ intervention, the study evaluation methods and the requirements of being involved. At the end of briefing event the school representative will be given written information for the head teacher along with a consent form. If schools are interested in being involved they will return the consent form signed by the head teacher.

All schools involved in the study will receive a £500 honorarium at the end of the study (i.e., once they have completed all evaluation measures) to encourage participation in the study and discourage dropout.

### Participant recruitment

Following school recruitment, all eligible participants within each school will be invited to take part in the study. All girls aged 11–14 years are eligible to take part and will be provided with an invitation pack, containing an invitation letter to parent(s)/guardian(s), parent/guardian information sheet, an opt out consent form for the parent/guardian (the parent/guardian only returns a signed opt out consent form if they do not want their child to participant) and a participant information sheet for the girls. If more than 80 girls are able to take part (i.e., have not returned an opt out consent form from their parent/guardian), 80 girls will be randomly selected using a computer generated number system. These 80 girls will provide verbal assent for study participation (at baseline and at each follow up visit).

### Sample size

Sample size calculations were performed to detect a mean difference of ten minutes of MVPA between the intervention and control groups. In order to detect a difference of 10 min/day between groups, assuming a standard deviation of 18 min in MVPA [31], a power of 90 %, a significance of 0.05, a cluster size of 56 girls and an intra-class correlation of 0.1, the sample size needed is 18 schools, increasing to 20 schools (10 schools per group) to allow for cluster attrition. To allow for 30 % loss to follow up and non-compliance with the accelerometer we will recruit 80 girls per cluster (1600 girls in total).

### Randomisation

Randomisation will occur after baseline assessments and will be carried out by the Leicester Clinical Trials Unit. Randomisation will occur at the school level (stratified by school size and proportion of Black and Minority Ethnic (BME) pupils) to receive either the ‘Girls Active’ intervention or carry on with usual practice (1:1).

### Intervention

The Youth Sport Trust (YST), an independent charity, have spent the last 10 years developing and refining initiatives aimed at engaging young girls in physical activity, physical education (PE) and sport. This expanse of work has evolved into a programme called ‘Girls Active’. ‘Girls Active’ is focused on providing a support framework to schools to review their physical activity, sport and PE provision, culture and practices to ensure they are relevant and attractive to all adolescent girls but with a particular focus on 11–14 year old girls (Key Stage 3). Furthermore, ‘Girls Active’ uses peer leadership and marketing to empower girls to influence decision making in their school, develop as role models and ‘sell’ physical activity to other girls. This process is underpinned by teachers and girls working together to understand the preferences and motivations of girls to take part in physical activity, sport and PE. ‘Girls Active’ is designed to be a flexible process for delivery but there are several key elements that underpin the programme. The elements are listed below.**Self-evaluation and mission analysis -** ‘Girls Active’ draws on the highly effective Mission 2012 review, planning and evaluation framework used by UK Sport to generate sporting success at the London Olympic and Paralympic Games. Using an adaptation of this Mission Analysis framework and a combination of marketing principles and youth leadership, it helps schools to review their existing culture and practice and to deliver an action plan tailored to their girls’ needs. This is an exercise that is carried out as a ‘pre-intervention and training’ task and allows schools to reflect on their practice that currently exists within their school.**Training for school leads –** Schools are invited to a one day orientation and training day to introduce schools leads to the resources and action planning This training covers the impact on school development plans and how using interventions such as ‘Girls Active’ can have a successful impact on attainment and achievement and on certain student groups that schools are trying to engage. The teachers also share challenges, successes and ideas with each other.**Package of resources –** At the training day schools receive a package of resources from the YST aimed at the teachers and the peer leadership and marketing group. This package contains resources such as marketing plans, an action planning guide, case studies, still and video images to stimulate discussion, and a ‘Making it Yours’ branding toolkit for peer leaders including a CD with logos, graphics and designs that peer leaders and teachers can use in their campaign.**Peer leadership and marketing group –** School leads can encourage, invite or ask for expressions of interest from Key Stage 3 girls (11-14 years) to volunteer to be part of this group. They are commonly girls who are not necessarily engaged in sporting and physical activities or particularly enthusiastic about participation, but are often girls who would be seen as leaders for non-sporting reasons and thus could have a positive influence on their peers. This group will influence decision making in their school, develop as role models, promote physical activity to other girls and run peer led physical activity sessions and events. Those involved in the peer leadership and marketing group will be provided with the branding toolkit and marketing ideas and will develop the campaign with support from the school lead.**Using the student ‘voice’ to develop and market ideas for change –** The ‘voice’ of the adolescent girl is key in decisions about physical activity, PE and sport in the school including the provision of changing facilities, kit, activity content, programming, inclusion and imagery. This process is underpinned by teachers and girls working together to come up with innovative and alternative physical activity and sports that they would like to participate in and can be incorporated in PE and extra-curricular activities. Most importantly this is a ‘different type’ of student voice, one that probably hasn’t been used before as it calls on the base of students who would not traditionally be involved in this type of provision.**On-going support and mentorship from the Health and Wellbeing School and the YST –** The local Health and Wellbeing School in Leicester, UK will offer support and mentorship to the intervention schools. This on-going support throughout the intervention phase could involve phone or email support and one to one visit support as is required. Their experience of developing and implementing similar programmes in schools that have little experience will be crucial to the on-going success of the ‘Girls Active’ programme. This mentor hub will also work alongside the programme manager responsible for ‘Girls Active’ within the YST.**Peer review day -** All schools will be invited to a peer review day to identify learning and practice; this will be led by the YST and the Health and Wellbeing School with the aim of teachers and peer leadership and marketing groups coming together to share ideas and solutions. This will tie in with the schools’ ‘mission analysis’ self-review and allow schools to progress those areas of development that have been highlighted through their involvement in ‘Girls Active’.**Funding for capacity building within the school -** There will be capacity payments made available to the schools involved in the ‘Girls Active’ intervention. Each of the intervention schools will be given capacity funding of £1000 in two £500 instalments.

The ‘Girls Active’ programme is guided by social cognitive theory (SCT) [32]. The literature on physical activity in young people suggests that addressing multiple levels of influence on behaviour (i.e. from the individual level to the environmental level), creating choice, increasing access and availability and physical opportunities to be active and fostering social support through positive peer relationships or friends are important and key during adolescence [8]. These constructs are all embedded within SCT and explicitly incorporated into the ‘Girls Active’ programme. Other core constructs of SCT such as observational learning, self-regulation and self-monitoring are also built into key intervention activities.

### Measurements

Data will be collected at three time points; baseline (February-April 2015), seven months after baseline (September-November 2015) and 14 months after baseline (April-June 2016). Trained researchers, following standard operating procedures, from University of Leicester and Loughborough University will collect data within schools and will be blind to the control and intervention allocation.

### Objectively measured physical activity

Participants will wear the GENEActiv Original accelerometer (Activinsights Ltd, Kimbolton, UK) continuously (i.e., 24 h/day) for seven days on their non-dominant wrist. This device has been found to be a valid and reliable objective measure of physical activity in young people [33]. Participants will be provided with a £5 gift voucher on return of their accelerometer with at least four valid days of data. The following variables will be calculated from the accelerometer data:Mean minutes of MVPA (overall and weekday and weekend split)Mean total volume of activity per day (overall and weekday and weekend split)Proportion of girls meeting the MVPA guidelines of 60 min per dayMean minutes of sedentary behaviour (overall and weekday and weekend split)

### Self-reported physical activity and sedentary behaviour

Self-reported physical activity will be captured using the Physical Activity Questionnaire for Adolescents (PAQ-A). The PAQ-A is a 7-day recall used to assess general physical activity levels during the school year using nine items [34]. The mode of commuting to and from school will be assessed using an adapted version of the questionnaire employed in the ENERGY project [35]. Sedentary behaviour will be captured using an adapted version the Adolescent Sedentary Activity Questionnaire (ASAQ) [36]. Participants will report the time they devote to a variety of different sedentary behaviours (e.g., watching TV, using the computer for fun, homework, reading, sitting around with friends etc.) in their free time on a typical weekday and weekend day.

### Demographic and anthropometric measures

Participants will be asked to report their date of birth, ethnicity and postcode. Postcode will be used to calculate the Index of Multiple Deprivation. Standing and sitting height will be measured using a portable stadiometer and weight and body fat with body composition scales (Tanita SC330S). Body mass index (BMI) will be calculated and converted to a BMI percentile based on UK reference data [37]. Stature (i.e., standing height), sitting height, leg length (stature-sitting height), age, and their interactions will be used to predict how many years a girl is from age at peak height velocity (APHV) [38], an indicator of biological maturity. APHV will be used categorise girls into maturity groups (early, average and late maturing).

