### Statistical analysis

This study will be analysed and reported according to the CONSORT statement for cluster RCTs. Data will be analysed on a complete case basis. The purpose of the primary analysis is to examine whether objectively measured MVPA at 14 months is higher in the intervention group than the control group. This will be examined using a linear multilevel model with MVPA as the outcome variable, levels to indicate the clustering of pupils within schools, a binary indicator for randomisation group as the explanatory variable, and terms for the stratification factors as confounders. Secondary outcomes, including those measured at other time-points, will be analysed using the same strategy with linear multilevel models used for continuous outcomes and logistic multilevel models used for categorical variables. Any changes in MVPA will be explored by extending the multilevel models to investigate whether the measured individual or school level characteristics mediate these changes. Sub-group analyses involving interaction and stratified analyses will be performed for non-active vs. active participants (defined as below or above the median MVPA level at baseline), single vs. mixed sex schools, white vs. BME participants and the degree of social deprivation based on the English indices of deprivation for the school location. These sub-group analyses will use the same models as the main analysis. Missing data will be replaced using multiple imputation methods. As a sensitivity analysis, we will repeat the analysis on both an intention to treat basis and per-protocol basis. To allow intention-to-treat analyses, missing data will be imputed using multiple imputation methods. The per-protocol analysis will only include those who were compliant with the protocol and follow-up visits. No formal interim analyses are planned. The baseline characteristics of those who did and did not drop-out will be compared to determine whether and how they differ. All tests and reported p-values will be two-sided. Estimates will be presented with 95 % confidence intervals.

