### Cost-effectiveness analysis

In this economic analysis we will fully cost the delivery of the ‘Girls Active’ intervention and the associated costs such as teacher time and other materials used. We will administer a diary to school leads asking them to complete a record of the additional time, or displaced time, taken to offer the ‘Girls Active’ intervention. We will use Local Education Authority teacher costs, accounting for overheads. From a public sector, multi-agency perspective, taking into account NICE guidance on economic evaluation of public health interventions [53], and based on our experience of evaluating the Wales National Exercise referral programme [54, 55], we will undertake a primary cost-effectiveness analysis of the ‘Girls Active’ intervention, using minutes of MVPA as the outcome effect, and a secondary cost per Quality Adjusted Life Years (QALY) analysis (embedded in a wider cost consequence analysis), using the Child Health Utility 9D (CHU-9D) as our source of utility weights [56]. The CHU-9D is a paediatric generic preference based measure of health related quality of life and consists of nine dimensions (worried, sad, pain, tired, annoyed, school work/homework, sleep, daily routine and ability to join in activities). This questionnaire will be completed at all measurement time points. We will pay particular attention to equity considerations through subgroup analysis (age, ethnicity, socio economic status and BMI at baseline). We will account for clustering in our analysis, producing cost-effectiveness planes and cost effectiveness acceptability curves (CEACs) in order to convey to policy makers the probability that ‘Girls Active’ is cost-effective at different payer thresholds. We will undertake 5,000 boot-strapped replications in order to generate confidence intervals around point estimates. In addition to this traditional approach we will also discuss the costs to this geographical area of “shifting the curve” – the cost of potentially shifting a proportion of girls from inactive to moderately active or moderately active to very active, depending on the findings of the trial. We will also undertake a sensitivity analysis to explore the impact of varying key factors on our results. Data on number of days absent from school, number of visits to the GP, school nurse and school counsellor will also be collected from participants.

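### BMI, one of two adiposity outcomes, is modelled linearly as a percentile without its baseline value; the BMI z score, adjusted for baseline, would be a free improvement.

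*Protocol article*

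**What the plan says.** The secondary objectives in the protocol article seek "Reductions in measures of adiposity (body mass index percentile, percent body fat"), so there are two adiposity outcomes. For the first, the section on demographic and anthropometric measures says that "Body mass index (BMI) will be calculated and converted to a BMI percentile based on UK reference data". For the second, the same section measures "weight and body fat with body composition scales (Tanita SC330S") and mentions no conversion to a reference scale.

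The statistical analysis section describes the primary model as a linear multilevel model with pupils nested in schools, a term for trial arm and terms for the stratification factors. Secondary outcomes follow the same strategy, with "linear multilevel models used for continuous outcomes". No baseline value of the outcome is among the listed terms. Neither a BMI z score nor any transformation of the percentile is mentioned.

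On population, "All girls aged 11–14 years are eligible to take part"; girls are not selected on weight. The effectiveness subgroups are baseline activity ("defined as below or above the median MVPA level at baseline"), single or mixed sex school, ethnicity and deprivation. Baseline BMI defines a subgroup only in the economic evaluation, which plans "subgroup analysis (age, ethnicity, socio economic status and BMI at baseline").

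**The concern.** A reference percentile is a non-linear function of the reference z score, squeezed towards 0 and 100. A linear model for the mean percentile therefore gives a change in a mid-range girl far more weight than the same change, in reference SD units, in a girl near the top of the scale. If the programme lowered BMI mainly in heavier girls, the estimated difference would understate it. No weight-status subgroup in the effectiveness analysis would bring it back.

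The model also lists no baseline value, although BMI is measured at baseline and would be expected to track strongly over 14 months. Leaving it out does not bias a randomised comparison, but it gives up precision.

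At stake is the sensitivity and interpretation of one secondary outcome.

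**Working it through.** **The plan's own figure.** The article gives no SD, target effect or power for BMI percentile. Its only calculation is for the primary outcome, to "detect a mean difference of ten minutes of MVPA". With SD 18, two-sided 5% and 90% power, n per arm = 2 × (18 × (1.960 + 1.282) / 10)² = 68.1. The design effect is 1 + 55 × 0.1 = 6.5. Schools per arm = 68.1 × 6.5 / 56 = 7.90, and 8.90 after adding one cluster per arm, so 9. A noncentral t calculation gives 90.1% power at 9 per arm. The 18 schools reproduce, and the scale used for BMI has no bearing on them.

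**Compression along the scale.** With percentile = 100 × Φ(z), a fall of 0.2 in z moves the percentile by 100 × [Φ(z) − Φ(z − 0.2)]:

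| Starting point | Points lost | Median figure ÷ this |
|---|---|---|
| z = 0 (50th) | 7.93 | 1.0 |
| z = 1.64 (95th) | 2.44 | 3.3 |
| z = 2 (97.7th) | 1.32 | 6.0 |
| z = 3 (99.87th) | 0.12 | about 66 |

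**Effect on what the model estimates.** The model estimates a difference in means, so the useful quantity is the standardised effect on the percentile divided by that on z. The inputs are assumptions, since the documents do not describe the BMI distribution: BMI z normal, with mean 0 to 0.7 and SD 1.0 to 1.2.

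*Every girl falls by 0.1 to 0.2 z.*
- Mean 0, SD 1, fall 0.1: the percentile falls 2.82 points against an SD of 28.82, giving 0.0979. On z it is 0.1/1 = 0.1. Ratio 0.98.
- Mean 0.7, SD 1.2, fall 0.1: 2.34/29.31 = 0.0798, against 0.1/1.2 = 0.0833. Ratio 0.96.
- All combinations tried: 96 to 98% kept.

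*Only girls above z = 1.33 (about the 91st centile) fall, by 0.25 z.*
- Mean 0, SD 1: 0.0089 on the percentile, 0.0228 on z. Ratio 0.39.
- Mean 0.7, SD 1.2: 0.0212 against 0.0626. Ratio 0.34.
- All combinations: 34 to 39% kept.

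The second scenario classes girls by where they would be at follow-up without the programme. If they are classed on baseline z instead, with an assumed baseline to follow-up correlation of 0.9, some have drifted back towards the middle. Simulating follow-up z as mean + 0.9 × (baseline − mean) + SD × √(1 − 0.81) × noise then gives 46 to 52% kept. The loss is still large, but nearer one half.

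**With baseline adjustment.** At a correlation of 0.9 on z, the residual SD on z is √(1 − 0.81) = 0.44 of the raw SD. The percentiles correlate slightly less (0.88 to 0.89 in simulation), so their residual SD shrinks less. For the uniform shift the ratio becomes about 0.90 to 0.94, a loss of about 6 to 10%.

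**The case against.** The strongest reply is that the percentile answers the question asked. The objective concerns adolescent girls in general, recruitment is not restricted by weight, and the intervention is aimed at whole schools. For a general shift the loss is a few percent. Nothing in the article predicts an effect confined to the heaviest girls. The percentile is also familiar to lay readers, and a difference in its mean between arms is a valid comparison. All of this stands.

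A reader might infer that adiposity as a whole is analysed on a compressed scale. The article does not support that: percent body fat is listed alongside BMI, is measured directly, and has no stated conversion to a percentile. A fall in fatness among heavier girls could show there, although that would not correct the BMI result.

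A reader might also take the extreme ratio, about 66 at z = 3, as typical of heavy girls. It is not: only about 0.13% of a reference population lies beyond that point, and at the 95th centile the ratio is 3.3.

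Finally, a full analysis plan that is not shown could add a z-score analysis or a baseline covariate. That softens the point but does not remove it, because the article itself names the percentile as the outcome and lists the model terms.

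**Conclusion.** The point holds as a minor improvement. The article fixes a bounded, compressed scale for BMI, puts it in a linear model, and lists no baseline term.

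The size depends on the pattern of effect. The loss is a few percent for a general shift, or about 6 to 10% once baseline is adjusted for. It is about two thirds if the effect is confined to girls above about the 91st centile, or nearer one half if they are classed on baseline. These figures rest on assumed normal BMI z distributions, shifts of 0.1 to 0.25 z and a correlation of 0.9, none of which is in the documents. The z score did no worse than the percentile in any scenario tried.

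It would go too far to infer that the plan hides the reduction its objective seeks. That would need the objective to be about the heaviest girls, which it is not, or the effect to be confined to them, which nothing in the article suggests. The primary outcome, the sample size and the main conclusion of the trial are untouched.

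**What to change.** In the section on demographic and anthropometric measures and in the secondary objectives, name the BMI z score from the same UK reference data as the analysed outcome. In the statistical analysis section, add baseline BMI z score as a covariate in the model for that outcome. Report the percentile descriptively by arm and time point, so that the familiar unit is kept.

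The cost is a change of wording. The z score comes from the same measurements and reference as the percentile, and the baseline value is already collected. The one drawback is a unit less familiar to lay readers, which the descriptive percentiles offset. A pupil without a baseline BMI would need a stated rule; the multiple imputation already planned could cover this. If the change comes after the outcome has been registered or published as a percentile, record it as a dated amendment made before the data are unblinded.
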